### Objectives {7}

The primary objective is to examine the effectiveness of case management for ABI compared to the care as usual on psychosocial well-being (emotional, participation and quality of life outcomes), self-efficacy and unmet needs. Secondary objectives are to explore cost-effectiveness and cost-utility (the balance of costs and gains in health and well-being) of case management compared to care as usual and to explore feasibility of case management for people with ABI and their family in terms of fidelity, dose delivered, dose received, reach and recruitment within its physical, social and political context. We expect case management to be effective and feasible, and we hypothesize that healthcare costs will rise at first and will be reduced in the long-term.

### Trial design {8}

This is a pragmatic prospective randomized controlled superiority trial with two parallel groups and repeated measures. Randomization will be performed as block randomization with a 1:1 allocation.

## Methods: participants, interventions and outcomes

### Study setting {9}

Recruitment of people with ABI will take place between November 2019 and July 2020 in three hospitals in the Netherlands: Deventer hospital (Deventer), St. Antonius hospital (Nieuwegein and Woerden) and Flevo hospital (Almere). Hospital staff will recruit people with ABI without further involvement in the study procedures, assessments will take place through home visits, via telephone or by sending questionnaires via mail.

### Eligibility criteria {10}

#### People with ABI

People with ABI are eligible for the trial if they comply with all of the following criteria at hospital discharge:
Acquired brain injury objectified by medical specialist (meningitis, encephalitis, hydrocephalus, subarachnoid hemorrhage, intracerebral or intracranial hemorrhage, ischemic stroke, transient ischemic attack, concussion, contusion, other head trauma).Aged 18 years or older.Living in the community prior to the injury.Discharged home or to a rehabilitation centre after hospital visit/admission.Sufficient command of the Dutch language to understand study procedures.Access to a computer and the internet (to use the monitoring tool, see ‘Intervention description {11a}’).Willing and able to give informed consent.

Exclusion criteria for people with ABI are:
A neurodegenerative disorder such as Parkinson’s disease or dementia (because of the progressive course of the disease).A diagnosis related to neuro-oncology (since an intensive care trajectory is already in place for this group).Discharge to a nursing home.

#### Family members

Family members are eligible when they comply with all of the following below. Off note, we speak of family members since usually the partner, a child or a parent is most likely to be the primary caregiver in case the person with ABI needs support, but friends or neighbours can also participate in this role if they are the ones most close to the person with ABI.
The person with ABI is eligible and willing to participate (i.e. family members can only participate if their relative with ABI is participating).They are (or would be if necessary) the primary informal caregiver; i.e. the person most close the person with ABI.Aged 18 years or older.Sufficient command of the Dutch language to understand study procedures.Access to a computer and the internet (to use the monitoring tool and questionnaires).Willing and able to give informed consent.

#### Case managers

Health care professionals are eligible for the role of case manager if they have professional experience in caring for people with ABI at bachelors’ level or higher (e.g. social workers, nurses, speech and language therapists and occupational therapists). They need to be available for at least 4–8 h per week for the duration of the project, willing to participate in the case manager training at the beginning of the project and in the monthly supervision meetings, and willing to register and document their case manager activities and experiences for research purposes. A formal application procedure will be followed; candidates are hired based on their resume, motivation and job interview by the project leaders.

### Who will take informed consent? {26a}

People with ABI and family members who are willing to participate will be visited at home by a trained research assistant, who will obtain informed consent prior to baseline assessment and after going over the study procedures. In case the home visit cannot take place, study procedures will be explained over the phone and informed consent is obtained by mail.

### Additional consent provisions for collection and use of participant data and biological specimens {26b}

On the consent form, participants will be asked if they agree to storage and use of their personal information for future research on brain injury or case management and if they agree to be approached for participation in future studies. By signing the consent form, participants give permission to the use of their data should they choose to withdraw from the study, for the research team to request injury-related information from their medical files and to share data with the regulatory authorities and the clinical research monitor of Maastricht University, where relevant. This trial does not involve collecting biological specimens for storage.

## Interventions

### Explanation for the choice of comparators {6b}

Case management is compared to the usual care as this is the current alternative.

### Intervention description {11a}

#### Case management

##### The framework

The framework for case management for ABI was developed based on a combination of the taxonomy for case management [24] and descriptions of case management for dementia in the Netherlands (e.g. [33–46]), because this form of case management is reasonably well integrated in the Dutch health care system. Such services can serve as a base for care innovations for people with ABI because of the shared focus on supporting people to adapt to the consequences of a disorder or disease in daily life [47].

Case management aims to support people with ABI and family member’s’ self-management of the consequences of ABI and psychosocial well-being, to prevent (escalation of) problems and to facilitate timely access to appropriate services. We propose the following case management elements:
Monitoring: tracking functioning and well-being of people with ABI and family members. In the present study, a digital monitoring system is used for this purpose (described below).Identification: identification of questions, problems and needs (based on monitoring) that hinder functioning and well-being at the time they emerge.Assessment: assessing the nature and severity of the presented problem, burden on and capabilities of the person with ABI and the family member, the role of their social network, making implicit or unmentioned questions and problems explicit, drawing conclusions about the core problem in the individual context.Information (psycho-education): providing information and education on the (impact of) ABI to assist understanding, information or education related to the question or problem (with a focus on capabilities to self-manage the problems), informing on available care and support services.Provision of support: guiding decision-making with regard to managing the problem, providing practical or psychosocial support for relatively mild problems (focused on maintaining or improving self-management).Referral: referring to more specialized care or support for relatively complex problems and guiding decision-making with regard to what available services to use.Coordination: supporting access to services, facilitating collaboration between different service providers and bringing about appropriate care when this is not available through the regular services.

Case management is person-centred and supposed to follow the ‘stepped care’ and ‘matched care’ principles, starting with the least complex form of care and support that meets the demand for help (stepped care), with the form and intensity individually built around the needs and capabilities of the person with ABI and/or the family member (matched care). Case manager activities may therefore vary from offering a listening ear or providing information and advice, to intensively coordinating longer-lasting specialist care. Case manager involvement also may vary in intensity over time, ranging from only monitoring to more intensive involvement.

Case management activities are community-based; they will take place at peoples’ home or other relevant places such as at work, or over the phone, via video calls or via email. While following the stepped care principle, case managers are flexible in the actions (interventions) they choose based on their own professional expertise, the links they make with available services (e.g. they are independent) and the way they create support when available services do not match people’s needs. Part of this study is mapping actual case manager activities onto the proposed elements and exploring whether this concept should be adjusted based on case manager and participant experiences, in order to move towards a more detailed description of what these elements entail in practice.

##### Monitoring tool (the ReMinder)

Participants receiving case management will be entered into a digital monitoring tool, called the ReMinder, developed by authors KHMJ and MD. This tool was originally developed to empower people who leave the hospital after a head trauma or stroke and their family to find information and get easy access to care in case of the development of problems caused by the injury on the long term. In the current research project, ReMinder is incorporated within OZO Verbindzorg, an online communication system that links different service providers through an online platform. The participant decides who gets access to the information in their OZO Verbindzorg account. For this project, this concerns sharing responses to the ReMinder questions (see below) with their case manager. Participants are in control of their account and may add other professionals involved in their care. They are in control of what information is shared with whom. All procedures are conducted according to the prevalent laws for personal data and privacy.

People with ABI and family members, each having their own account, will automatically receive an email every 3 months, which allows them to enter the monitoring system and to answer two questions: (1) Do you experience problems as a consequence of brain injury? (2) Are you (Is your loved one) able to do all the things you were (he/she was) doing prior to the brain injury? Both questions can be answered with yes or no. If the participant responds ‘yes’ to question 1 and/or ‘no’ to question 2, they are directed to a 32-item questionnaire asking about functioning in the areas of health, daily life, activities, social contacts and consequences of ABI. This questionnaire was composed by the developer of the ReMinder (authors KHMJ and MD), inspired by the Checklist for Cognitive and Emotional Consequence of Stroke (CLCE-24 [48]), the Utrecht Scale for Evaluation of Rehabilitation-Participation (USER-P [49];), Outcome Questionnaire (OQ-45 [50];) and the life domains of the ICF: International Classification of Functioning, Disability and Health (ICF-model). Participants fill out the questionnaires as self-report. Family members fill out the questionnaire reporting about the person with ABI and five extra questions about his or her own well-being. In order to facilitate easy access to the case manager, at completion of the 32-item questionnaire participants will be asked if they would like to have contact with the case manager (yes/no). In addition, people with ABI and family members also have the opportunity to ask a question to the case manager directly at any time within the online environment.

The responses are visible to the case manager to keep track of functioning and well-being of the person with ABI. The case manager will contact those participants who explicitly indicate that they would like to get in touch. For participants who do not initiate contact with their case manager themselves, the case manager determines whether to contact the participant after the second time participants have filled out the ReMinder (i.e. 3 months after the first ReMinder questionnaire). The decision to get in touch with the participant will generally be based on whether responses indicate that certain problems have not been resolved (consistently low scores in one or more areas), a deterioration in scores, or profound discrepancies in scores between the person with ABI and their family member.

##### The case manager

The case manager is a fixed contact person; building a relationship is desirable because of the complexity of learning to live with ABI within the individual context, and to prevent the person with ABI and their family from having to tell their story over and over again. A back-up case manager will be assigned as well, who will be involved when the primary case manager is unavailable and who can serve as a sparring partner for the primary case manager.

The case managers form three teams, one in each region. Teams are composed of professionals from different disciplines and with varying backgrounds; some have been working in clinical/rehabilitation settings, others in community outreach, and their experience with support and treatment approaches may be focused on cure or on care. Two of the teams include a peer support worker.

Case managers will participate in a 4-day training prior to the start of the study. The training has a coaching character, promoting team members to draw upon each other’s knowledge and experience. During the training, case managers learn to see beyond one’s own specific professional discipline, get to know the professional background of the other team members and are coached in learning from each other to best support people with ABI and their family. Regular supervision meetings are organized with case managers within regions at least every 2 months, and between regions twice a year.

#### Care as usual

The usual care differs depending on the regional structures and collaborations. In all regions, limited structured care is available for people who suffered a stroke, mostly for secondary prevention purposes, with a limited duration of 1 year. No structural care is provided for other types of ABI. People with ABI can make use of different forms of care that may or may not involve professionals with expertise on ABI, such as physiotherapy, occupational therapy or social work, but patients usually need to take initiative to find and access these services either themselves or through their general practitioner.

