### Sample size {14}

Power calculation was based on the primary outcome measure Hospital Anxiety and Depression Scale (HADS). A study evaluating a monitoring/psycho-educational intervention in patients with possible ABI due to cardiac arrest showed to be effective in improving both anxiety and depressive symptoms with a group difference on the HADS of 3.25 points, corresponding to Cohen’s *d* effect size of 0.36 [73]. With an alpha of .05 and power value of 80%, a sample size of 194 is required to detect such between-group effect in the post-intervention measurement. This number can be adjusted for the correlation between baseline and follow-up data, since baseline measures will be entered in the model as an independent variable, by multiplying the sample size by 1 − *R*^2^ (R is the population correlation between the dependent variable (post-intervention) and the pre-intervention measurement) [74]. *R* is estimated to be at least 0.5, making the sample size 194 × (1 − 0.5^2^) = 146. Taking a drop-out rate of 30% into account, at least 209 people with ABI should be recruited. For each participating person with ABI, the family member who is or would be acting as the informal caregiver will be asked to be enrolled in the study as well. The number of participating family members will not exceed the maximum of 209.

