## Statistical methods

### Statistical methods for primary and secondary outcomes {20a}

#### Effectiveness

Multilevel modelling will be used to assess the improvement of case management participants over time compared to care as usual. Primary analysis involves entering time, group and their interaction (exposure) as fixed terms. Separate analyses will be performed to assess 24-month outcomes for the subgroup of participants for whom this data is available. Sensitivity analysis will be performed by extending the resulting models with covariates, controlling for the effects of age, gender and level of education. Covariates will be kept in the model as long as they contribute significantly to the model. Significance of the fixed regression effects will be tested using the appropriate *t*-test (*α* = .05).

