### Methods for additional analyses (e.g. subgroup analyses) {20b}

Subgroups will be formed based on type of injury (stroke vs. other types) and severity, for which length of hospital stay will be used as a proxy (based on the distribution of the sample). Even though the subgroups are likely to be too small to draw firm conclusions, we will analyse this exploratively because the usual care for stroke is already better organized than for other types of brain injury (possibly lowering the additional gains of case management over care as usual for stroke compared to other types of brain injury) and because those with moderate to severe ABI may have more to gain from case management than those with mild ABI.

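### Injury type, which the protocol itself ties to usual care and to the expected gain, is left out of the allocation and the primary HADS model

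*Protocol article*

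**What the plan says.** All references are to the protocol article.

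- **Care as usual** (under Intervention description {11a}): "In all regions, limited structured care is available for people who suffered a stroke, mostly for secondary prevention purposes, with a limited duration of 1" (one year). For the rest, "No structural care is provided for other types of ABI".
- **Methods for additional analyses {20b}**: an exploratory subgroup analysis of stroke versus other injury is planned because stroke care is already better organised, "possibly lowering the additional gains of case management over care as usual for stroke compared to other types of brain injury". The section concedes that the subgroups will probably be too small for firm conclusions.
- **Sample size {14}**: one effect is used for everyone. "A study evaluating a monitoring/psycho-educational intervention in patients with possible ABI due to cardiac arrest showed to be effective", with "a group difference on the HADS of 3.25 points", taken as d = 0.36. The section continues: "With an alpha of .05 and power value of 80%, a sample size of 194 is required". This becomes 146 after baseline adjustment with R = 0.5, and 209 after 30% drop-out.
- **Trial design {8}** and **Sequence generation {16a}**: 1:1 allocation in blocks of six, with no stratification factor named.
- **Statistical methods {20a}, Effectiveness**: "Primary analysis involves entering time, group and their interaction (exposure) as fixed terms". The sensitivity covariates are age, gender and education, each retained only if significant.
- **Other study parameters** (under Outcomes {12}) and **Plans for assessment {18a}**: type of injury is collected at baseline.

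**The concern.** The protocol names one baseline variable as a determinant of what the control arm receives and as a possible modifier of the treatment effect. It collects that variable for every participant. It then gives it no role in the allocation, the primary model or the named covariate sensitivity analysis, and uses it only for exploratory subgroups. The covariates it does name are ones for which it offers no comparable reason.

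Two modest things are at stake. First, if injury type predicts HADS, a chance difference in stroke share between the arms adds noise to the primary contrast that a single model term would remove. Second, the sample-size section does not say how its single d relates to a mixed population in which the protocol itself thinks the gain may be uneven.

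**Working it through.** **1. Reproduce the stated sample size.** Inputs from Sample size {14}: d = 0.36, alpha .05, power 80%, R = 0.5, drop-out 30%.

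- Two-sample t-test, one-sided .05: 97 per arm, total 194, as stated. Two-sided .05 gives 123 per arm, total 246, so 194 reproduces only as one-sided. The protocol does not state sidedness.
- 194 × (1 − 0.5²) = 145.5, rounded up to 146. Then 146 / 0.7 = 208.6, rounded up to 209.
- Power at 73 per arm (normal approximation, one-sided): 0.36/√0.75 × √(73/2) = 2.51, and Φ(2.51 − 1.645) = 0.807. The noncentral t gives 0.804.

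**2. Chance imbalance in stroke share.** With 209 randomised as 104 and 105, the 95% range of the difference in stroke share s is 1.96 × √[s(1 − s)(1/104 + 1/105)]. The protocol does not give s, so it is assumed.

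- s = 0.3 or 0.7: 1.96 × 0.0634 = 0.124
- s = 0.5: 1.96 × 0.0692 = 0.136

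That is about 12 to 14 percentage points either way.

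**3. What such an imbalance could do to the HADS contrast.** The shift is the imbalance times the stroke-versus-other difference in HADS. That difference is not given, so a range is assumed. The implied SD is 3.25/0.36 = 9.03 points. At the upper imbalance of 0.136:

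- assumed difference 0.1 SD: 0.014 SD, or 0.12 points
- 0.3 SD: 0.041 SD, or 0.37 points
- 0.5 SD: 0.068 SD, or 0.61 points

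These compare with a target difference of 3.25 points. They would be smaller to the extent that baseline HADS, once in the model, already carries the injury-type difference.

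**4. What a smaller stroke effect would do to power.** Let f be the fraction of the effect kept in stroke, and suppose that people without stroke have d = 0.36. The average is then 0.36 × [s·f + (1 − s)]. Both s and f are assumed. One-sided .05, 73 per arm, normal approximation:

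| f | s = 0.3 | s = 0.5 | s = 0.7 |
|---|---|---|---|
| 1 | 80.7% | 80.7% | 80.7% |
| 0.75 | 75.1% | 71.0% | 66.5% |
| 0.5 | 68.8% | 59.4% | 49.5% |

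**5. The same unevenness with no loss of power.** If 0.36 is the average over the mix, then at s = 0.5 and f = 0.75 the non-stroke effect is 0.36/0.875 = 0.411, the stroke effect is 0.75 × 0.411 = 0.309, and power stays at 80.7%. The protocol does not say which reading of 0.36 it intends.

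**The case against.** A reader might infer three stronger things. The document supports none of them.

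*That the 80% power does not hold for the mix enrolled.* Every figure below 80% in step 4 rests on an assumed stroke share and an assumed stroke effect. The protocol gives neither and says only that a smaller gain is possible. A pragmatic trial may size on an average effect, and step 5 shows that uneven effects alone cost nothing.

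*That 0.36 is the effect against no structured care, because it comes from cardiac-arrest patients.* The Care as usual section describes the regions of this trial, not the control care in the cited study, which is not visible here. The diagnoses listed under Eligibility criteria {10} do not name hypoxia or cardiac arrest either. So 0.36 cannot be assigned to the non-stroke group.

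*That an unequal stroke share biases the comparison.* Both arms keep access to the same care (Relevant concomitant care {11d}). Randomisation balances injury type in expectation, and the error rate of the test already covers chance differences.

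Calling these two separate comparators would also go too far. The stroke care is limited, aimed mainly at secondary prevention, and ends after a year, while follow-up runs to 18–24 months. The subgroup section already recognises the issue, and injury type could enter the missing-data sensitivity analysis under {20c} if it is associated with missing outcomes.

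What survives is narrower. None of these provisions places injury type in the primary model, whose terms the article does state, and the protocol's own reasoning makes it a more natural covariate than the three it names.

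**Conclusion.** The point holds as a low-cost improvement to a stated model. The protocol says that usual care, and possibly the gain, differ by injury type, collects the variable, and leaves it out of the allocation, the primary model and the named sensitivity covariates. The chance difference in stroke share is about 12 to 14 percentage points (95% range), assuming a stroke share of 30 to 70% and about 104 randomised per arm. Its effect on HADS depends on how strongly injury type predicts the score, which the document does not give; under the differences assumed above it is about 0.1 to 0.6 points.

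On power, the supported statement is conditional: the stated figure applies if 0.36 is the average over the people enrolled, and falls if a smaller stroke effect pulls the average down. An illustration is 71%, with half the participants having stroke and keeping 75% of the effect, on the one-sided basis that reproduces 194. Separately, the undiluted d at two-sided .05 also happens to give about 71% with 146 analysed; that concerns sidedness, not injury mix.

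**What to change.** **Main change, Statistical methods {20a}, Effectiveness.** Add injury type (stroke versus other) as a prespecified fixed covariate in the primary HADS model, exempt from the rule that drops non-significant covariates. Sample size {14} assumes that baseline HADS enters as an independent variable. If baseline is instead modelled as one of the repeated responses, include injury type by time as well, because a main effect alone would hardly alter the group-by-time contrast.

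**Optional, {20b}.** Estimate the exploratory stroke and non-stroke effects from a group-by-injury-type term in the same model, with confidence intervals. The intervals will be wide, and this mainly sharpens what is already planned.

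**Optional, {14}.** State that d = 0.36 is taken as the average effect over the enrolled mix, and that power falls if the average is lower.

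The cost is a few sentences and one or two model terms. The data are already collected, and no recruitment or change to allocation is needed.
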